## Study part B

Patients fulfilling the additional inclusion criterion for study part B will be either randomised into one of the two study arms of the trial or – if they do not consent to participate in the trial – will be assigned to the second control group. The intervention group will receive telephone counselling sessions every 4 to 6 weeks during the first 12 months after recruitment. The intervention and control groups will additionally receive standardised patient questionnaires (see above) after 6, 12 and 18 months. The diabetes therapy during the course of the intervention study, including occasioned diagnostic and therapeutic measures as well as incidence of potential diabetes-related complications (e.g. myocardial infarction) and hospital admissions, will be documented using the standardised follow-up GP questionnaires (see above) after the end of the intervention (at 12 and 18 months).

After completion of study part B the patients will be also followed-up in the context of the epidemiological cohort study.

## Analysis of blood parameters

The measurement of the primary outcome (HbA1c) and other parameters will be conducted in all participants (study part A and B) at recruitment and follow-ups.

In participants of study arm B an additional measurement of the primary outcome will be conducted after 12 months (end of intervention).

The blood collection will be carried out in the participating practices. Overall about 30 ml blood per patient will be drawn (EDTA + serum). The handling of the blood samples in the practices, the shipping to and the analyses conducted by the central laboratory in the Ludwigsburg-area as well as the storage of the blood samples will be carried out according to standard operating procedures.

Those blood samples that are not immediately needed for the determination of HbA1c will be shipped and transferred to the Division Clinical Epidemiology and Aging Research at DKFZ for the scientific investigation of further markers (including genetic markers) that could be important for the onset and progress of diabetes mellitus and potential complications. The samples will be preserved without time limit, in order to allow for specific laboratory analyses with improved technical possibilities and considering new scientific findings in the future. The biological material that will be preserved without time limit will be completely anonymised after completion of data collection to render inference to the individual study participant impossible. If necessary, specimens will be shipped to external project-related collaborating partners with specific expertise in special laboratory analyses that cannot be conducted at the DKFZ. Commercial utilisation interests will be excluded for that matter.

## **8. Accompanying therapy**

Not relevant.

## **9. Security laboratory (if relevant)**

Not necessary.

## **10. Termination criteria**

### **10.1 Individual termination criteria**

- withdrawal of consent,
- inability to continue participation,
- In the case of withdrawal from the study the respective participant has the right to demand the complete elimination of his pseudonymised data. For this, all possibilities of

withdrawal will be listed and explained and separately asked at the time of withdrawal.

## **10.2 Termination criteria for the study**

- lack of willingness to participate among practices,
- insufficient recruitment of patients,
- for the trial no interim analysis is intended that could justify a preliminary termination of the study.

## **11. Statistical design**

Study part A:

The statistical examination particularly includes the following analyses:

- a thorough description of the whole cohort regarding parameters relevant for diabetes (amongst others: age, sex, duration of disease, medication, body weight, comorbidity, life style factors) at recruitment,
- epidemiological analyses regarding determinants and prognostic markers in patients in the overall cohort after completion of further follow-up measurements.

Study part B:

Power calculation:

Assuming that both in the intervention and in the control group about 4 patients are lost in the course of the study (n=120 per group), with 2-tailed testing, equal variance, a standard deviation of 1.0, a significance level of  $\alpha=0.05$ , the following statistical power results regarding the decrease in HbA1c (see next page):

| Decrease of HbA 1c of ... %-points
in the intervention group | Power       |
|----------------------------------------------------------------------------|-------------|
| 0,1                                                                        | 0,12        |
| 0,2                                                                        | 0,34        |
| 0,3                                                                        | 0,64        |
| 0,4                                                                        | 0,87 |
| 0,5                                                                        | 0,97 |
| 0,6                                                                        | 0,99 |
| 0,7                                                                        | 1,00 |
| 0,8                                                                        | 1,00 |
| 0,9                                                                        | 1,00 |
| 1,0                                                                        | 1,00 |

The proposed study therefore has sufficient power to detect clinically relevant changes in HbA1c with the selected sample size.

The scientific evaluation will investigate the following outcomes:

*Primary outcome: **HbA1c***

HbA1c is the main outcome of diabetes therapy and reflects the quality of metabolic control in the past three months.

HbA1c will be determined at the beginning of the study as well as immediately and 6 months after the end of the intervention in all trial participants.

*Secondary outcomes:*

Diabetes mellitus is a chronic disease in which the further course of health (incidence of complications and sequelae) largely depends on a preferably integrated medical care as well as on lifestyle factors. Therefore the following secondary outcomes will be evaluated besides the primary outcome HbA1c:

- lipid metabolism control
- blood pressure
- body weight, physical activity, smoking
- health-related quality of life
- incidence of diabetes-related complications

- hospital admissions
- mortality.

The primary working hypothesis is that supportive telephone counselling in these patients helps improving the primary outcome of diabetes therapy (HbA1c). The secondary working hypothesis is that, as consequence, also secondary outcomes (diabetes-related complications, hospital admissions, mortality etc.) will improve.

The statistical examination includes the following analyses:

- a thorough description and comparison of control and intervention group regarding diabetes-related parameter (amongst others: age, sex, duration of diabetes, medication, body weight, comorbidity, life style factors),
- a thorough description and comparison of control and intervention group regarding the primary and secondary outcomes at the end of the intervention,
- analyses on the association of intervention and changes in outcomes during long-term follow-up (sustainability of the intervention),
- a thorough description and comparison of eligible patients unwilling to participate in the trial and of control and intervention group regarding the primary and secondary outcomes at the end of the intervention (assessment of external validity/generalisability of results).

The comparison of change in HbA1c in both study groups using multiple linear regression and adjusting for potential confounders will be the main analysis of the intervention study (study part B).

Further analyses will be conducted, also adjusting for potential confounders and using multivariate regression models (multiple linear regression or Cox proportional hazards models, depending on the outcome). These will be based on a priori formulated protocols for analyses. All analyses will be conducted using the statistical software SAS and under the supervision of the project leader.

Gender specific aspects will be considered in sub-group analyses by doing sex-stratified analyses. That way, different factors can be considered in the multivariate models, regarding which men and women may differ (health behaviour, perceptions of illness/health, etc).

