### **Study part B**

In a sub-group of cohort study participants additionally: Open randomised controlled trial with about 124 patients each in intervention and control group. According to the „comprehensive cohort design“, patients who are eligible but do not agree to participate will be followed up as non-randomised control group (no telephone counselling; approx. 64 patients).

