### **Study part B**

In order to prevent a distortion of results by potential confounders, patients will be individually randomised. The randomisation will be conducted centrally in the study centre at the DKFZ for all eligible patients of the participating GP practices. The web-based patient randomisation service for multi-centre clinical trials of the Institute for Medical Informatics, Statistics and Documentation at the Medical University of Graz, Austria, will be used for the randomisation (<http://www.randomizer.at>). Because of the limited number of study participants and the number of participating GP practices, the minimisation method is used to ensure an equal distribution of potential influencing factors in the two randomised study arms. As influencing factors the GP practice (as study centre) and age and sex of the participants will be considered.

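### Sex differences are to be examined by separate models in men and women, with no stated comparison of the treatment effect between them and with covariates allowed to differ

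*Protocol*

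**What the plan says.** The last paragraph of section 11 (Statistical design) names the method for sex and the reason for choosing it: "Gender specific aspects will be considered in sub-group analyses by doing sex-stratified analyses. That way, different factors can be considered in the multivariate models". The factors meant are ones that may not be alike in the two sexes; health behaviour and perceptions of illness are its examples.

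The paragraph follows the part B analysis text. There the primary comparison is one pooled analysis of HbA1c change, "using multiple linear regression and adjusting for potential confounders will be the main analysis of the intervention study", and further analyses may use linear or Cox regression under separate a priori analysis protocols, which are not shown. The power table in the same section covers the whole trial only. Section 5 makes sex a minimisation factor: "As influencing factors the GP practice (as study centre) and age and sex of the participants will be considered".

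The protocol names no arm-by-sex interaction, no confidence interval for the difference between the sex-specific effects, and no caution on reading them.

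**The concern.** Whether counselling works differently in men and women is a question about the difference between two effects. The stated method yields an estimate and a p-value for each sex and stops there. Each stratum holds only part of the sample, so one can reach significance and the other miss it by chance, even when the true effect is the same in both.

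The freedom to use different covariates adds a second problem, whose size depends on the model:

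- In a linear model for HbA1c with baseline covariates, the adjusted estimate in each sex still targets the mean difference between arms in that sex. Different covariates then mainly change precision, which alone can move one sex across the significance line.
- In a Cox model, hazard ratios conditional on different covariates are different quantities.
- If a covariate is measured after randomisation, part of the effect may be adjusted away in one sex and not in the other. The paragraph does not restrict the factors to baseline values. Its health-behaviour example overlaps with physical activity and smoking, which section 11 lists as secondary outcomes.

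At stake is the reading of a sub-group result. The main trial conclusion does not depend on it.

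**Working it through.** **Inputs from the protocol.** Section 4 gives the allocation: "Open randomised controlled trial with about 124 patients each in intervention and control group". Section 11 gives the loss and the analysed number, "about 4 patients are lost in the course of the study (n=120 per group", and the remaining terms, "with 2-tailed testing, equal variance, a standard deviation of 1.0", with alpha 0.05.

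**Assumptions.** The documents give no sex split. I take 50:50, with 35:65 as the other end of the range. Minimisation on sex supports equal numbers of each sex in the two arms. SD is 1.0 within each sex, and any precision gained from covariates is ignored.

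**Step 1: the plan's own figures.** Two-sided t test, noncentrality d / (SD × √(2/n)), n = 120 per group, 238 df. For d = 0.1 to 0.6 this gives power 0.121, 0.339, 0.639, 0.870, 0.971 and 0.996. The table states 0.12, 0.34, 0.64, 0.87, 0.97 and 0.99. It is reproduced.

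**Step 2: power within one sex.** The same formula with n = 60 per arm (50:50), or with 42 and 78 per arm (35:65).

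**Step 3: chance that exactly one sex is significant when the true effect is the same in both.** The strata are independent, so the probability is p1(1 − p2) + p2(1 − p1).

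| True effect in both sexes (%-points) | Power, whole trial | Power per sex, 50:50 | Exactly one sex, 50:50 | Power per sex, 35:65 | Exactly one sex, 35:65 |
|---|---|---|---|---|---|
| 0.3 | 0.64 | 0.371 | 0.467 | 0.274 / 0.461 | 0.482 |
| 0.4 | 0.87 | 0.584 | 0.486 | 0.441 / 0.699 | 0.524 |
| 0.5 | 0.97 | 0.775 | 0.349 | 0.620 / 0.874 | 0.411 |
| 0.6 | 0.996 | 0.903 | 0.175 | 0.776 / 0.961 | 0.246 |
| 0.7 | 1.00 | 0.967 | 0.063 | 0.887 / 0.991 | 0.120 |

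Worked for 0.4 at 50:50: exactly one = 2 × 0.584 × 0.416 = 0.486; both = 0.584² = 0.34; neither = 0.416² = 0.17. Significance in one sex only is then the most probable single pattern, although no difference exists.

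**Step 4: what a direct comparison can show.** SE of the interaction = SD × √(2/n_men + 2/n_women), with n per arm.

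- At 50:50: √(2/60 + 2/60) = 0.258. The difference detectable with 80% power is (1.960 + 0.842) × 0.258 = 0.72 %-points. At 35:65 the SE is 0.271 and the difference 0.76.
- Power at 50:50 (normal approximation) for a true between-sex difference of 0.3, 0.4 and 0.5 is 0.21, 0.34 and 0.49.
- To detect a between-sex difference of 0.4 with 80% power, n per sex per arm = 4 × (2.802/0.4)² = 196.2, so 197, or 394 per arm against the 120 analysed here.

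**The case against.** A reader might infer that the trial intends to compare significance between men and women and to report that counselling works in one sex only. The protocol states no such rule. Neither the objectives in section 2 nor the working hypotheses in section 11 include a sex difference. How the results would be read is a risk, not something the plan announces.

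A reader might also infer that stratified models can never show a sex difference, or that their estimates are not comparable at all. Neither follows. The strata are independent, so the two estimates can be subtracted and given a confidence interval, and in linear models with baseline covariates they target like quantities. The protocol also says only that factors can differ, not that they must.

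The size depends on the effect. The expression 2p(1 − p) cannot exceed 0.50, and an effect of 0.4 puts p near that maximum; by 0.7 the chance at 50:50 is 0.06. Under no effect in either sex, the chance that at least one is significant is 1 − 0.95² = 0.0975, but that is not the error rate of a claim that the sexes differ and should not be quoted as one.

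Two further points are fair. The unseen analysis protocols may add a comparison. The paragraph carries no part A or part B label, and sex-specific covariates suit prognostic modelling well.

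What remains is that this protocol chooses the stratified method, justifies it by the freedom to vary covariates, and places it directly after the trial analysis without a between-sex comparison. That is a stated choice of method, not merely a detail left for later.

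**Conclusion.** The point holds as a minor one. The stated method does not itself test whether the treatment effect differs by sex, and it allows covariate sets that make the two estimates harder to compare, above all in Cox models or with covariates measured after randomisation. For common true effects of 0.3 to 0.4 %-points, there is about an even chance (0.47 to 0.52) that exactly one sex is significant. The chance falls to 0.35–0.41 at 0.5 and 0.175–0.246 at 0.6. These figures rest on the assumed sex split and on SD 1.0 in each sex.

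The documents do not support the stronger statement that a false sex-specific claim will follow. The pooled primary analysis is untouched.

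**What to change.** For the part B treatment comparison, replace the stratified models with one model on all randomised patients containing arm, sex, arm-by-sex and one common pre-specified set of baseline covariates. Report the interaction with its 95% CI and derive the effects in men and in women from that model. Base any statement of a sex difference on the interaction, label it exploratory, and state the limited precision computed above. Sex-specific covariates may stay in the part A prognostic models, and the paragraph should say which part each rule covers.

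The cost is a change of wording: sex is already recorded and used in the minimisation, so no new data are needed. What is given up is sex-specific covariate choice in the trial comparison. The change does not make the trial able to detect a modest sex difference. It makes that limit visible and holds the false-positive rate of a sex-difference claim at the nominal 5%.

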## 12. Ethical and legal aspects

The investigation will be conducted in accordance with the Declaration of Helsinki in the current version from 1996, as well as on the guidelines for Good Epidemiological Practice (GEP) adopted by the German Working Group for Epidemiology (Deutsche Arbeitsgemeinschaft für Epidemiologie, DAE) that are based on the Declaration of Helsinki, and according to the code of medical ethics of the Chamber of Physicians of the state Baden-Württemberg in its respective current versions. The participation of patients in the study is voluntary. The consent to participate can be withdrawn at any time, for any reason and without any disadvantages for further medical care. The study does not involve any risks for its participants. The participants have sufficient time to look into the objectives and process of the study at home. They have the chance to pose questions to the study secretariat or the participating GPs. After their questions have been answered, subjects willing to participate may sign the written informed consent form.

The nature and consequences and especially the possible benefit and potential risks of the planned study will be explained to the patients before beginning of the study both in written and oral form. Their consent will be documented with a signature on the informed consent form. At withdrawal from the study the patient is entitled to request the elimination of already collected (data) material.

Before the beginning of the study, the study protocol will be submitted to the ethics commission of the Medical Faculty of the University of Heidelberg for review. Inclusion of patients/subjects will not start before having received a written affirmative vote from the ethics commission.

The names of the patients and all other confidential information are subject to medical confidentiality and the regulations of the German data protection law (Bundesdatenschutzgesetz, BDSG). If necessary, a transfer of patient data will only occur in pseudonymised form. Commercial utilisation interests will be excluded for that matter.

### *Patient questionnaires, informed consent forms and transfer contract*

The questionnaires to be filled in by study participants carry a unique ID number. Study participants will be asked to fill in name, address and date of birth on the cover page of the questionnaire. After receipt of the questionnaire at the DKFZ the cover page with the person-identifying information will be separated from the rest of the questionnaire, which carries the ID number only. The further storage and processing of person-identifying data will be performed completely separately from the processing of the study data.

The person-identifying information on the cover page will be processed on a stand-alone

personal computer in the study secretariat, which is not connected to a network. This computer provides programs and files for the management of the study participants. Only staff in charge of study organisation has access to this computer. The computer is secured with special security software (Safeguard Easy), for which a password is needed to gain access.

After removal of the personal ID number, the cover page of the questionnaire will be stored exclusively in a separate steel locker in a room with special locking system in the study secretariat. Only a limited and nominated number of persons will hold a key to this room.

The informed consent form and the transfer contract will include name and signature of the study participant. After receipt at DKFZ, they will be stored exactly as described for the cover page of the questionnaire (see above).

#### *Blood samples*

The blood samples will be collected, shipped, stored, processed and analysed exclusively in pseudonymised form (after the end of data collection only in anonymised form), i.e. only tagged with the ID number.

## Appendix

[figure not shown]

Supplement: Protocol S1 — Trial Protocol. (PDF) [file pone.0077954.s002.pdf]
